# Rehabilitation access and effectiveness for persons with back pain: the protocol of a cohort study (REHAB-BP, DRKS00011554)

**DOI:** 10.1186/s12889-017-4588-x

**Published:** 2017-07-14

**Keywords:** Medical rehabilitation, Back pain, Access barriers, Effectiveness, Propensity score matching

## Abstract

**Background:**

Back pain is one of the most common chronic diseases in Germany and has a major impact on work ability and social participation. The German Pension Insurance (GPI) is the main provider of medical rehabilitation to improve work ability and prevent disability pensions in Germany. However, over half of the persons granted a disability pension have never used a medical rehabilitation service. Furthermore, evidence on the effects of medical rehabilitation in Germany is inconclusive. Consequently, this study has two aims: first, to determine barriers to using rehabilitation services, and second, to examine the effectiveness of medical rehabilitation in German residents with chronic back pain.

**Methods:**

In 2017 a postal questionnaire will be sent to 45,000 persons aged 45 to 59 years whose pension insurance contributions are managed by the GPI North or the GPI Central Germany. In 2019 respondents who report back pain in the first survey (*n* = 5760 expected) will be sent a second questionnaire. Individuals will be eligible for the first survey if they are employed, have neither used nor applied for a rehabilitation programme during the last 4 years and neither received nor applied for a disability pension. The sample will be drawn randomly from the registers of the GPI North (*n* = 22,500) and the GPI Central Germany (*n* = 22,500) and stratified by sex and duration of sickness absence benefits. Barriers to rehabilitation services will be related to socio-demographic and social characteristics, pain and attitudes to pain, health and health behaviour, healthcare utilisation, experiences and cognitions about rehabilitation services and job conditions. Propensity score matched analyses will be used to examine the effectiveness of rehabilitation services. Data on use of medical rehabilitation will be extracted from administrative records. The primary outcome is pain disability. Secondary outcomes are pain intensity and days of disability, pain self-efficacy, fear avoidance beliefs, self-rated health, depression, healthcare utilisation, self-rated work ability and subjective prognosis of employability, sickness absence benefits, and disability pensions.

**Discussion:**

This study identifies barriers to use of rehabilitation services and determines the effectiveness of medical rehabilitation for patients with chronic back pain.

**Trial registration:**

German Clinical Trials Register (DRKS00011554, January 26, 2017).

**Electronic supplementary material:**

The online version of this article (doi:10.1186/s12889-017-4588-x) contains supplementary material, which is available to authorized users.

## Background

With 12-month prevalence rates of more than 75% [1], back pain is one of the main health problems in German adults [2]. National health surveys indicate that 25% of women and 17% of men reported experiencing chronic back pain (CBP), i.e. back pain almost every day for at least 3 months, during the last 12 months [3]. Back pain is more prevalent in women, in older people and in people with less education [1, 3]. Use of health care services, sickness absence, and disability pension payments mean that illness has a high cost [2].

The World Health Organisation (WHO) deemed rehabilitation essential to enabling people with disabilities or chronic diseases to participate in work and society, but also identified unmet needs [4]. In Germany, age standardised utilisation of medical rehabilitation for musculoskeletal disorders decreased over the 14-year period between 2001 and 2015 from 11.9 per 1000 to 8.7 per 1000 in men and from 10.6 per 1000 to 7.7 per 1000 in women. Moreover, the proportion of disability pensioners with musculoskeletal disorders who did not undergo medical rehabilitation before their disability pension was granted increased over the 5-year period between 2007 and 2012 (males: 47.5 to 48.3%; females: 41.0 to 45.0%) [5, 6].

Previous international research studies have reported various barriers to using rehabilitation services, i.e. factors that prevent persons from using rehabilitation services despite an obvious need for them. For example, a systematic review [7] identified a range of financial, structural, personal and attitudinal determinants of access to rehabilitation services in the United States, but it is questionable whether these findings would transfer to the German context. In Germany, rehabilitation for working-age people is provided mainly by the German Pension Insurance (GPI). The GPI is a compulsory pension insurance scheme. Workers contribute to a pension scheme which is administered by the GPI. If workers reach the age of 65 years (gradually increasing to 67 years by 2031), the GPI pays a monthly pension based on their pension contributions. People who have a permanent disability that prevents them from working receive a disability pension until they become eligible for an old age pension. The GPI provides rehabilitation services on the principle ‘rehabilitation before pension’, i.e. they aim at avoiding paying disability pensions. The GPI offers about one million rehabilitation programmes per annum. Usually the prerequisite for access to rehabilitation is a claim by the person in question. The claim will be appraised by the GPI to determine the need for rehabilitation. Only post-acute rehabilitation (about one third of all rehabilitation measures) makes a simplified procedure for gaining access to medical rehabilitation possible.

During the last two decades, a number of studies have attempted to address the problem of unmet rehabilitation needs in Germany, either by asking people eligible for rehabilitation services or important stakeholders about barriers to using them [8–13] or by comparing users and non-users to identify determinants of rehabilitation utilisation [13–19]. According to these studies, the main predictor of rehabilitation utilisation appears to be impaired health, manifested as poor subjective health [8, 11, 14–17], functional impairment or impairment in activities of everyday life [11, 19], chronic conditions [11, 19], poor work ability [11, 18], long sickness absence [8, 11, 14, 19], and greater use of medical care services [11, 14]. Though these findings indicate that use of medical rehabilitation services is linked to substantial health problems affecting work ability, they do not give insight into the barriers to using rehabilitation services. Other studies have found that subjective rehabilitation need, rehabilitation intention and plans for utilising rehabilitation services predicted use of services [17]. These variables may be proxy measures for the level of information about rehabilitation services and thus lack of awareness may represent a barrier to use of services. This suggestion is supported by the finding that the probability that an individual would request rehabilitation services was increased by a higher self-efficacy, i.e. the belief of being able to apply for a medical rehabilitation [17]. Further cross-sectional findings also indicate the relevance of self-rated job insecurity [8, 9, 11, 13], the recommendation of the attending physician [8, 10–12, 17, 20] and perceived family support [10–12, 17, 20]. Positive attitudes toward rehabilitation services were more salient in former rehabilitants or persons who planned to participate in a rehabilitation programme in the near future [8, 11, 19, 20]. Previous research studies have produced inconsistent findings on the roles of sex, age, and socio-economic background in the use of rehabilitation services [8, 11, 13–15, 20]. In the case of people with CBP intention to use and actual use of rehabilitation services may be influenced by job situation, work conditions, conflict between work and family roles and coping strategies, but so far these potential barriers have not been investigated through longitudinal research. Our first research goal is therefore to analyse a comprehensive set of barriers to accessing rehabilitation via a prospective design, using a sample large enough to provide a clear picture of the determinants of use of medical rehabilitation services.

The second research goal relates to the effectiveness of rehabilitation services. Attending physicians, who are important stakeholders when requesting medical rehabilitation, should base their advice about medical rehabilitation on the best current evidence [21]. Although international research has shown that multimodal medical rehabilitation has a beneficial impact on various outcomes (work ability, pain, quality of life, participation) [22–27], the setting and context of these studies were different from the 3-week inpatient rehabilitation programmes that are usual in Germany and so a separate evidence base is needed to demonstrate the effectiveness of German rehabilitation programmes. However, evidence on the health-related effects of German medical rehabilitation programmes for patients with CBP is, at best, contradictory [28, 29]. A previous small, single-centre randomised controlled trial tested the efficacy of medical rehabilitation in patients with CBP using a waiting list control group. Jäckel et al. [30] found short-term effects (4-week follow-up) on pain, anxiety and depression. The design did not enable testing of long-term effects. A more recent randomised controlled trial by Hüppe et al. [31] used a smart approach in which patients suffering from chronic musculoskeletal disorders who had impairments indicative of a need for rehabilitation had been actively supported to request for rehabilitation services. Within 6 months of study entry, 69% of the intervention participants, but only 20% of the controls, participated in a 3-week inpatient rehabilitation programme, but there were no group differences in any of the primary and secondary outcomes at the 6- and 12-month follow-ups. It should be noted, however, that the effects of rehabilitation were tested in a population that only opted to pursue rehabilitation after receiving additional support and counselling designed to encourage them to do so. Lower grade evidence for the effectiveness of rehabilitation is available from case series (observational studies without controls). These studies reveal minor to moderate improvements in several outcomes [32, 33]. However, the randomised controlled trial by Hüppe et al. [31] indicated that comparable patients who do not use rehabilitation services might show similar improvements. Whilst these findings might justify restricting access to medical rehabilitation, remarkable efforts have been made to improve rehabilitation services over the last several years. These include the development of evidence-based therapy standards designed to improve the quality of multi-professional treatment and the provision of active therapies [34], implementation of modern patient education interventions [35, 36], the development of work-related medical rehabilitation [37–40], and more emphasis on aftercare and follow-up sessions to maintain behaviour and attitude changes [41, 42]. Randomised controlled trials and controlled clinical trials have shown that these modifications do improve outcomes compared to conventional medical rehabilitation.

According to the demands of evidence-based medicine, the lack of evidence may itself be a major barrier to the utilisation of rehabilitation services. It follows that to justify increased utilisation of rehabilitation services in the future we need high-quality investigations into the effectiveness of rehabilitation services. From a health service research perspective there needs to be a focus on rehabilitation under real-life conditions and its long-term effects through comparisons with patients who do not receive rehabilitation services. Large-scale, randomised controlled trials with long-term follow-up periods are not feasible due to the legal foundations of rehabilitation, so appraisals of the outcomes of medical rehabilitation must be based on data from cohort studies. To our knowledge, this study is the first attempt to investigate the effects of German medical rehabilitation services for persons with CBP, under routine conditions and via a large cohort study using propensity score matching.

The study protocol has been prepared according to the Standard Protocol Items: Recommendations for Interventional Trials (SPIRIT) checklist [43].

## Methods

### Study design

The study is designed as a cohort study. Persons with back pain will be identified via a preliminary survey and then followed up. Back pain patients who complete a medical rehabilitation will be compared with back pain patients who do not participate in a medical rehabilitation programme. Propensity score matching will be used to match controls to treated patients and to estimate unbiased effects of medical rehabilitation.

Baseline data will be assessed to identify persons with back pain and to analyse barriers to using rehabilitation services. Follow-up data will be assessed at the beginning of the third year of the study to determine the effectiveness of medical rehabilitation. Administrative data from the GPI registers will also be used. Given the observational design no-one will be blinded before, during or after the trial.

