### Treatment

#### Control

Participants in the control group receive no medical rehabilitation and are identified through propensity score matching.

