#### Intervention

Participants in the treatment group will take part in a medical rehabilitation programme based on current treatment standards and guidelines for the rehabilitation of back pain [34]. The medical rehabilitation programmes are multimodal and consist of three to 4 h of therapy per day, including sports and exercise therapy, physiotherapy, occupational therapy, massage and other physical therapies, social and psychological counselling, patient education, pain management and relaxation training. They focus on the functional limitations of the musculoskeletal system and aim to restore physical abilities in order to promote participation in work and daily life. The duration of the rehabilitation programme is determined initially by the GPI North and GPI Central Germany and is usually about 3 weeks. Rehabilitation services may be provided as inpatient or outpatient programmes. Patients with musculoskeletal diseases spend 23 days at the rehabilitation centre on average [44], with sports exercise being the most frequent therapy during the 3-week rehabilitation (>13 h per week, 74% of all therapies) [44]. The rehabilitation centre and the patient may arrange to extend the programme. The patient may stop the rehabilitation programme ahead of schedule on request.

Applications to use rehabilitation services, the related decisions, and the utilisation of these services are documented in the GPI registers and data relating to the first year of the study will be extracted from these records.

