### Statistical analysis

#### Analysing barriers to rehabilitation utilisation

To identify barriers to the utilisation of medical rehabilitation services we will compare persons with back pain who complete a medical rehabilitation with persons with back pain who do not. We will identify barriers to use of rehabilitation services across the entire course of the rehabilitation process, from recognition of need for rehabilitation and applying for a medical rehabilitation programme, to applying successfully for a grant, participating in a rehabilitation programme and completing the programme. Different barriers apply to each step and these will be identified by analysing group differences in baseline values of the outcome and control variables at each stage of the process. The first step in the analysis will be univariate analyses: *t* tests and analyses of variances for continuous variables, Mann–Whitney *U* tests for ordinal variables and chi-squared tests for binary variables. The second step will consist of logistic regression analyses to identify the most important predictors of rehabilitation intention, rehabilitation application, acceptance onto a rehabilitation programme and use of rehabilitation. In the third step we will estimate generalised structural equation models to describe the direct and indirect effects of potential barriers.

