#### Propensity score matching

Rehabilitation participants and untreated subjects will be matched by propensity scores to achieve a balanced sample and enable calculation of unbiased estimates of effectiveness [67–72]. The propensity score is the conditional probability of receiving the treatment under evaluation (i.e. the medical rehabilitation programme) given the vector of observed background variables. Matching by propensity scores allows one to obtain a sample in which the treated and untreated groups are balanced, if there is sufficient overlap between their propensity scores. Propensity score matching also allows one to avoid the dimensionality problem that affects conventional direct matching procedures involving multiple variables, e.g. age, sex, socioeconomic state, depression, work ability, by reducing the matching requirement to a single dimension.

The propensity score will be estimated using a logistic regression model including all variables that are associated with treatment allocation. For every treatment case three persons with a similar propensity score will be selected from the larger pool of non-treatment cases. Re-sampling with replacement will be used to reduce bias. If it is necessary to achieve a balanced sample, a caliper of one-quarter of the propensity score will be used during re-sampling. Additional matching schemes will be used in the sensitivity analysis.

Standardised percentage bias will be calculated as an indicator of bias before and after matching due to differences in observed sample characteristics. This is the difference between sample means in the intervention and control groups relative to the square root of the average of the sample variances in both groups [73]. Multiple imputations will be used to fill in missing data before propensity scores are estimated. The propensity scores for each record will be averaged across the completed datasets and propensity score matching will be performed with these averaged scores [74].

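### The Study design section sets completers of rehabilitation against non-participants, while other sections define the treated group by participation; on the former, early stoppers fall in neither effectiveness group

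*Protocol article*

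**What the plan says.** All places are in the protocol article.

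- **Study design** gives the effectiveness contrast: "Back pain patients who complete a medical rehabilitation will be compared with back pain patients who do not participate in a medical rehabilitation programme". The next sentence promises that propensity score matching on this contrast will yield unbiased effects.
- The **Control** section keeps anyone with rehabilitation out of the comparison group: "Participants in the control group receive no medical rehabilitation and are identified through propensity score matching".
- The **Intervention** section describes the treated group without any condition that they finish: "Participants in the treatment group will take part in a medical rehabilitation programme". Further on, the same section allows early stopping: "The patient may stop the rehabilitation programme ahead of schedule on request".
- **Sample size estimation** derives the treated group from an 8% utilisation rate and arrives at 276 rehabilitants against 828 untreated controls.
- **Propensity score matching:** "Rehabilitation participants and untreated subjects will be matched by propensity scores". The score itself is the probability of receiving the programme given observed background variables.
- **Estimating the treatment effect** names the average effect in treated cases as the quantity of interest.
- **Analysing barriers to rehabilitation utilisation**, which serves the other aim, will "compare persons with back pain who complete a medical rehabilitation with persons with back pain who do not". It lists "participating in a rehabilitation programme and completing the programme" as separate steps.

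The article gives no completion rate and does not say how early stoppers enter the effectiveness analysis.

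**The concern.** The article gives two different treated groups for one analysis: completers (Study design) and participants (Intervention, Sample size estimation, Propensity score matching). They differ by the patients who start and stop early. The barrier section separates participation from completion, so the word in Study design cannot be dismissed as a loose synonym for taking part.

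The choice matters because completion becomes known only during the programme. Requiring it filters the treated group on tolerance, motivation or early course, and no such filter applies to controls. The right comparators for completers would be controls who would have completed had they started, and a score built on baseline variables can identify them only as far as those variables predict completion.

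Three things are at stake: the promise of an unbiased estimate, the Background's aim of measuring rehabilitation as it works in routine care (where some patients stop early), and the meaning of the effect in the treated, which would become an effect in completers. If the wording stays unreconciled, the treated group could also be chosen after the data are seen.

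**Working it through.** **1. Where an early stopper goes**

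| Section | Treated or index group | Comparator | Patient who starts and stops |
|---|---|---|---|
| Study design, with Control | completers | non-participants, no rehabilitation | in neither group |
| Intervention, Sample size estimation, Propensity score matching | participants, users, recipients | untreated | treated |
| Barrier analysis (separate aim) | completers | all who do not complete | comparator |

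For effectiveness there are two candidate treated groups. The barrier row answers a different question.

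**2. The plan's own figures**

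Inputs (Abstract; Sample size estimation): 45,000 mailed, response 40%, linkage consent 80%, back pain 40%, utilisation 8%, follow-up response 60%, standardised mean difference 0.2, two-sided alpha 0.05.

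- With back pain: 45,000 × 0.40 × 0.80 × 0.40 = 5,760, as stated.
- Rehabilitants: 5,760 × 0.08 = 460.8.
- With follow-up: 460.8 × 0.60 = 276.5, stated as 276. Controls: 3 × 276 = 828.
- Power = Φ(0.2 / √(1/276 + 1/828) − 1.96) = Φ(2.878 − 1.96) = 0.821. The noncentral t gives 0.820. The stated 0.82 is reproduced.

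Since 8% is a utilisation rate, 276 counts everyone who uses rehabilitation, not only those who finish.

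**3. Power if only completers count**

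The completion share c is assumed; treated = 276 × c, with 1:3 matching and the effect held at 0.2.

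| c | Treated | Controls | Power |
|---|---|---|---|
| 1.00 | 276 | 828 | 0.82 |
| 0.95 | 262 | 786 | 0.80 |
| 0.90 | 248 | 744 | 0.78 |
| 0.80 | 221 | 663 | 0.73 |

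**4. Shift in the estimate**

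Let d_c and d_s be the benefits of completers and stoppers over their matched controls, in SD.

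- All starters: c·d_c + (1 − c)·d_s.
- Completers only: d_c.
- Difference: (1 − c)·(d_c − d_s), that is, the share stopping times the gap that remains after baseline adjustment.

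Both inputs are assumptions.

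| Share stopping | Residual gap (SD) | Shift (SD) | Shift / 0.2 |
|---|---|---|---|
| 5% | 0.3 | 0.015 | 7.5% |
| 10% | 0.5 | 0.050 | 25% |
| 15% | 0.5 | 0.075 | 37.5% |
| 10% | 0 | 0 | 0% |
| 10% | −0.25 | −0.025 | −12.5% |

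The last row covers patients who stop because they have improved; dropping them lowers the estimate.

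**The case against.** The strongest defence is that the completer wording stands in one overview sentence. The sections that govern matching and estimation contain no completion condition, and the sample size rests on utilisation. A reader might infer from Study design that a completers-only analysis has been adopted; the article does not support that, because most of its text points to participants. What remains is a contradiction on who is treated, located in the sentence that states the contrast.

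A reader might also infer that the effect is inflated. The article gives no stop rate, no reasons for stopping and no outcomes for stoppers, so neither sign nor size follows from it. In addition, under a completers definition controls would be matched to the completers' own scores. Where stoppers differ on measured baseline variables in the score (Table 2 includes pain, depressive symptoms, self-efficacy and work ability), the control mean moves too and that part cancels. This objection stands, and it is why the gap in the calculation must be read as what remains after baseline adjustment.

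The barrier analysis might be read as placing early stoppers among the effectiveness controls, or as adding a third treated group. It does neither: its index group is again completers, it serves a separate aim, and the Control section excludes anyone with rehabilitation from the effectiveness controls.

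Finally, handling of early stoppers is often left to an analysis plan, and none is shown. That would excuse silence. It does not excuse two conflicting definitions that are both written down.

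**Conclusion.** The concern holds as an internal contradiction with a possible bias attached. On the Study design wording, taken with the Control and Intervention sections, early stoppers are in neither effectiveness group, and selection after treatment start enters a comparison that is promised to be unbiased. Upward bias is plausible if stoppers do worse, but it is not shown.

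The size is illustrative only: 0.015-0.075 SD if 5-15% stop and completers retain a residual advantage of 0.3-0.5 SD, with both ranges assumed. Against a target as small as 0.2 SD, the upper part of that range would matter; a zero gap would do no harm, and a reversed gap would lower the estimate. The loss of power is modest at high completion (0.80 at 95%, 0.78 at 90%) and larger at 80% (0.73). The stated 0.82 is correct for all who use rehabilitation.

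**What to change.** In Study design, replace completion with any rehabilitation start (participation) documented in the pension insurance register within the extraction window. Use the same treated group in Intervention, Sample size estimation, Propensity score matching and Estimating the treatment effect. Report completers against matched controls as a sensitivity analysis only. Keep completion as the last step of the barrier analysis, whose groups need not change.

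The cost is mainly wording. The planned 276 against 828 and the power of 0.82 stay as they are, because the 8% already refers to utilisation. There are two downsides. The estimated effect may be slightly smaller. The register extract must also identify starts as well as completions: the Intervention section says that utilisation is recorded but does not say that the two are recorded separately, so this should be confirmed with the data holders. The barrier analysis needs the same distinction in any case.
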